### Patients: inclusion and exclusion criteria

Inclusion criteria are adults (>18 years old), men and women, with chronic Chagas disease diagnosed by two distinct Chagas serology tests (indirect immunofluorescence and ELISA), and complicated by HF. For the purpose of this study, HF diagnosis will be based on current or past symptoms compatible with HF and associated with underlying structural heart disease and left-ventricle ejection fraction under 55%, as measured by an echocardiogram. Exclusion criteria are: any comorbidities that significantly affect cardiac performance, such as coronary artery disease, moderate or severe heart valvular disease, left-ventricle hypertrophy, or congenital heart disease; comorbidities that limit survival, such as malignant tumors or HIV; failure to obtain informed consent; inability to perform six-minute-walk test; significant cognitive impairment; pregnancy; concomitant participation in other intervention trials; or NYHA functional class IV.

### Interventions: pharmaceutical care vs. standard care

The pharmaceutical care applied in this trial will be based on Dáder methodology. The Dáder method for pharmaceutical care is a systematic process developed by the Research Group of Pharmaceutical Care at the University of Granada, Spain [32]. This method includes patient education about cardiovascular drugs, patient counseling about lifestyle modifications, assessment of drug compliance, identification of underuse of appropriate drugs, optimization of drug dosage, and identification of the use of inappropriate drugs, to enable the pharmacist to deliver treatment recommendations to physicians and contribute to relieving DRPs [32] and improved quality of life [21,23].

Those patients randomized to standard care will receive all prescription medications from the pharmacist and basic instruction on how to use them.

### Outcomes

The primary endpoint of this trial will be an increase in the quality of life. Heart disease may impose important limitations on patients’ daily activities that often affect their functional and general health status [21]. Quality of life will be evaluated using the 36-item short-form (SF-36) [33] and the Minnesota Living with HF Questionnaire (MLHFQ) adapted by Carvalho *et al*. [34]. The SF-36 will be measured in all eight subscales: physical functioning, physical role, bodily pain, general health, vitality, social functioning, emotional role, and mental health. The two summary measures are the Physical Component Summary and the Mental Component Summary score. Items scores related to each subscale are coded, summed, and scaled from 0 (worst possible health state) to 100 (best possible health state) [23,33,35,36]. The MLHFQ is one of the most widely used questionnaires to evaluate quality of life of patients with HF. It is made up of 21 items that cover HF-related physical, psychological, and social impairments. The patient’s perception of such impairment is assessed on a scale ranging from ‘none’ (a score of 0) to ‘very much’ (5). The total MLHFQ score is obtained by adding the scores for all 21 items (range, 0 to 105), where a higher score indicates a worse quality of life [37].

The secondary endpoints evaluated will be incidence and types of DRPs, physical functional capacity, and compliance. Drug-related problems will be identified case by case, based on the classification of the Brazilian Pharmaceutical Care Consensus [38]. They will be classified by evaluating three distinct criteria of pharmacotherapy: indication, effectiveness, and safety [30,38]. Among DRPs, suspected ADRs will be classified according to Naranjo’s algorithm [39]. All identified DRPs will be reported in patients’ medical records. Another secondary endpoint will be physical functional capacity. All patients will have their functional capacity measured by the six-minute-walk test. The test will be performed at the beginning of protocol and after 12 months of follow-up. The test will be conducted on three consecutive days, at the same time and followed by the same evaluator. It will take place along a closed corridor, 33 m long. Walk tests will be performed at least 2 hours after patients’ meals. Patients will be instructed by a cardiologist or designed professional to walk as much as possible for 6 minutes. Patients will be oriented to adjust their walking speed between relatively easy and slightly tiring. The test will measure the maximum distance each patient can walk in the corridor [40-42]. Patients’ compliance to medical treatment will be measured using self-reports of medication adherence on the Morisky scale [43]. This simple four-question survey assesses the likelihood that patients take their medications as prescribed. The questions will be: ‘Do you forget to take your medications? Are you careless about the time at which you take your medications? Do you stop taking your medications when you feel better? Do you stop taking your medications when you feel worse?’ Each ‘yes’ answer is given a score of 1, and each ‘no’ a score of 0. Those patients scoring 0 will be considered adherent, and those scoring 1 to 4 will be considered nonadherent [43].

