**Methods/design:**

A prospective, single-center randomized clinical trial will be conducted in patients with Chagas heart disease complicated by heart failure. A total of 88 patients will be randomly assigned into two parallel groups: an intervention group will receive standard care and pharmaceutical care, and a control group will receive only standard care. Both groups will be subjected to a follow-up period of 12 months. The primary outcome of this trial is the evaluation of quality of life, measured by the 36-item short-form and the Minnesota Living with Heart Failure Questionnaire. Secondary outcomes include drug-related problems, exercise tolerance as measured by the standard six-minute-walk test, and compliance.

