### Statistical methods

The EpiData [46] and Statistical Package for the Social Sciences [47] applications will be used for data entry and analysis, respectively. The statistical calculations will be performed on an intention-to-treat basis, where patients will be analyzed as initially randomized. Continuous variables will be expressed as mean ± standard deviation. The Kolmogorov-Smirnov test will be used to test sample distribution. The analysis strategy will be based on differences of MLHFQ and SF-36 scores, DRPs outcome, and six-minute-walk test results between the control and intervention groups. For quality-of-life questionnaires and the six-minute-walk test, the Student’s *t* test will be used if sample distribution proves to be normal. Otherwise, the Wilcoxon rank-sum test will be used. For DRPs and compliance, cumulative incidence and relative risks will be estimated with their respective 95% confidence intervals, and will be used to test differences. The null hypothesis will be rejected at *P <* 0.05.

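### The quality-of-life primary endpoint covers up to 11 scores under one P < 0.05 rule, with no single primary score and no success rule, so the false-claim rate is not fixed.

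*Protocol article*

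**What the plan says.** The Abstract of the protocol article states: "The primary outcome of this trial is the evaluation of quality of life, measured by the 36-item short-form and the Minnesota Living with Heart Failure" (the MLHFQ). The Outcomes section puts the endpoint as "The primary endpoint of this trial will be an increase in the quality of life". It names both instruments together and gives neither precedence: "Quality of life will be evaluated using the 36-item short-form (SF-36) [33] and the Minnesota Living with HF Questionnaire (MLHFQ"). The scores it lists are these:

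- SF-36 subscales: "The SF-36 will be measured in all eight subscales".
- SF-36 summaries: "The two summary measures are the Physical Component Summary and the Mental Component Summary score".
- MLHFQ: "The total MLHFQ score is obtained by adding the scores for all 21 items (range, 0 to 105").

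No overall SF-36 score is defined.

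The Statistical methods section compares the two groups on the scores of both questionnaires by t test or rank-sum test. Its decision rule is in the singular: "The null hypothesis will be rejected at *P <* 0.05".

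The Sample size calculation section uses a 10.3-point difference on the SF-36, with Table 1 means of 52.8 and 63.1. It does not say which SF-36 score these are, and it uses a one-sided 1% level. The Discussion expects a gain of at least ten points on both questionnaires and ranks neither first.

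**The concern.** A primary hypothesis needs one variable, or several variables with a rule for combining them. Here the endpoint is a concept measured by up to 8 + 2 + 1 = 11 scores, while the decision rule is written as if there were one null hypothesis. Two things follow.

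First, the type I error of the primary claim cannot be stated, because it depends on a success rule that is not given. If the rule is settled after the results are seen, a favourable score can be picked out.

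Second, a mixed result has no defined reading. One SF-36 subscale might be significant while the MLHFQ total is not, and the article does not say whether the trial has then succeeded.

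This is more than detail left to an analysis plan. The article itself fixes a multi-score primary endpoint and a single-hypothesis rule, and the two do not fit together.

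**Working it through.** **Does the sample size identify the primary score?** Inputs from the Sample size calculation section and Table 1: difference 10.3, SD 10.9, significance 1%, power 95%, 40 per group.

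n per group = 2 (z_alpha + z_power)² (SD / difference)², with (10.9 / 10.3)² = 1.120.

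- Two-sided 1%: 2 × (2.576 + 1.645)² × 1.120 = 39.9, so 40. This reproduces the plan's figure.
- One-sided 1%, as the text states: 2 × (2.326 + 1.645)² × 1.120 = 35.3, so 36. This does not reproduce it.

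The figure of 40 therefore fits one test of one SF-36 score at two-sided 1%. The Outcomes section lists ten SF-36 scores and no total, so the powered variable cannot be matched to any one of them. The calculation points to the SF-36 but does not settle the primary score.

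**False-claim rate if any one significant score suffices.** Each score is tested at two-sided 0.05. A false claim of better quality of life arises only on the favourable side, so its nominal rate is 2.5%.

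Independent scores:

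- 11 scores, favourable side: 1 − 0.975^11 = 24.3%. Either side: 1 − 0.95^11 = 43.1%.
- 2 scores, favourable side: 1 − 0.975² = 4.9%. Either side: 1 − 0.95² = 9.8%.

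The article gives no correlations between scores. Equal positive correlations were therefore assumed, and 400,000 sets of normal test statistics were simulated with no true effect:

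| Assumed correlation | 11 scores, favourable side | 11 scores, either side | 2 scores, favourable side | 2 scores, either side |
|---|---|---|---|---|
| 0.3 | 19.1% | 37.6% | 4.8% | 9.5% |
| 0.5 | 15.2% | 30.3% | 4.6% | 9.1% |
| 0.7 | 11.1% | 22.4% | 4.2% | 8.4% |
| 0.9 | 6.6% | 13.1% | 3.5% | 7.1% |

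The nominal rate is 2.5% in the favourable-side columns and 5% in the either-side columns.

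**At the 1% level of the sample size.** With each of 11 scores tested at two-sided 1%, the either-side rate is 1 − 0.99^11 = 10.5% if independent, 7.9% at correlation 0.5 and 5.7% at 0.7. These are smaller, but still above 1%.

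**If all scores must succeed.** The chance that every score is falsely significant cannot exceed the chance for one, so there is no inflation.

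**What the remedies cost in power.** These figures use 40 per group and the Table 1 effect (10.3 points, SD 10.9).

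- One named score: 98.8% at two-sided 0.05, 95.1% at two-sided 1%, 97.1% at one-sided 1%.
- Two scores at 0.025 each: 97.6%.
- Eleven scores at 0.05 / 11 = 0.0045 each: 91.7%. Restoring 95% would need 46 per group before dropout.

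**The case against.** A reader might infer that, as the plan is written, any one of the eleven scores carries the primary claim, so that the error is 43% and far above the stated level. The documents do not support this:

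- **No any-one rule is stated.** The wording joins the questionnaires with a plain conjunction, in both the Abstract and the Discussion. If both or all had to succeed, nothing would be inflated.
- **Eleven is the upper count.** The Outcomes section describes how the SF-36 is scored. It does not say that every subscale and summary carries the primary hypothesis. One score per questionnaire is an equally open reading, and it gives much smaller figures.
- **The 43% answers a different question.** It includes false findings against the intervention, while the endpoint is an improvement. It also assumes independence, although ten of the scores come from one questionnaire and two of those are summary measures.
- **The stated level is itself unsettled:** 0.05 in Statistical methods, one-sided 1% in the sample size.

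All four points stand and limit the size of the problem. It can also be said that adjustment methods belong in an analysis plan that is not shown. That is fair for the choice of adjustment method. It does not cover the identity of the primary score, which the protocol must fix and which this article leaves open while stating a decision rule for it.

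**Conclusion.** The concern holds as a fault of specification: the primary score and the success rule are not defined. Its size is conditional. If any one significant score may support the claim, the favourable-side error against 2.5% is about 15%, 11% and 7% for 11 scores at correlations of 0.5, 0.7 and 0.9, with 24% under independence as an upper bound. For one score per questionnaire it is about 3.5% to 5%. The two-sided equivalents against 5% are 30%, 22% and 13% for 11 scores, and 7% to 10% for two.

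These figures rest on assumed equal correlations and on tests at two-sided 0.05. Inflation disappears only under a rule that all scores must succeed, which the article does not state. The lack of a defined reading for a mixed result does not depend on any of these assumptions.

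**What to change.** Amend the protocol, and the analysis plan if there is one, before unblinding:

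1. Name as the single primary score the specific SF-36 score on which the Table 1 means (52.8 and 63.1) are based. The article does not identify it, so the sponsor must trace it in the cited heart-failure study and confirm that it is one of the scores listed under Outcomes.
2. State one alpha and one sidedness for that test, reconciling the 0.05 in Statistical methods with the one-sided 1% in the Sample size calculation.
3. Test the MLHFQ total next, in fixed sequence at the same alpha, and only if the primary score succeeds.
4. Report the remaining SF-36 scores as secondary estimates with confidence intervals and no confirmatory claim.

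Splitting alpha between two scores, or requiring both to succeed, would also resolve the ambiguity if stated in advance. The fixed sequence keeps the full alpha for the powered score.

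The cost is wording: the planned 40 evaluable patients per group still give at least 95% power for the named score under the Table 1 assumptions at any of the three levels checked. The downside is that the other scores can no longer carry the primary claim on their own. If the SF-36 score misses, even a strong MLHFQ result is not confirmatory.

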### Ethical issues

This study was approved by our local Committee for Ethics in Research (IRB) under the number 0034.0.009.000-11 and is registered at ClinicalTrials.gov under number NCT01566617 [44]. The IPEC IRB membership includes multidisciplinary representation as well as community representation. It is registered at the National Committee for Ethics in Research-MOH [45] and operates according to the Brazilian Ethics in Human Research Regulations.

#### Protection against risk

The informed consent process will be conducted according to good clinical practices. The potential study patients will sign an informed consent form after reading it, receiving adequate explanations, and understanding the study objectives and procedures. Illiterate patients may bring in relatives or friends to read for them, testify, and sign the consent form: if this is not possible, we can enroll a patient, and a witness will sign the consent form. The formal informed consent process will be accomplished and documented before any other study-related procedures. Adequate time will be allowed for the patient to ask questions. All aspects of the study will be explained to the patients, including, but not limited to, potential risks and benefits, and the amount of time required from the patient, including the number of study visits expected. All patients will be informed that participation is voluntary, that refusal to participate will involve no penalty or loss of benefits to which the patient is otherwise entitled, and that the patient may discontinue participation at any time without penalty or loss of benefits to which the patient is otherwise entitled.

The investigators will see patients at regular intervals. Patients who miss a scheduled study visit will be contacted by telephone to schedule a new visit. Case report forms will identify patients only by the study number. All records identifying patients by name and information linking patients’ names with study ID numbers will be kept in locked rooms in locked cabinets and will be accessible only to study personnel. We will provide patients with the names and telephone numbers of the principal investigator and sub-investigators, and they will be advised that they are allowed to make reverse-charge telephone calls. Information regarding the patient’s medical history will be obtained with the patient’s consent. Regarding this proposal, the procedures are considered to offer minimal risks for the patients. The patients may derive direct benefits derived from research and the knowledge acquired may potentially improve the health care of other patients suffering from Chagas disease. Therefore, the benefits of this research will fall into two major categories: benefits to patients and benefits to society. Patients will not receive any kind of remuneration, but will be reimbursed for travel expenses and meals.

#### Data and safety monitoring plan

The IPEC IRB will reevaluate the research project at intervals appropriate to the degree of risk but not less than once a year. Periodic review of the research activity is necessary to determine whether the risk/benefit ratio has shifted, whether there are unanticipated findings involving risks to patients, and whether any new information regarding the risks and benefits should be provided to patients. At the time of initial review, the IPEC IRB will determine whether an independent data and safety monitoring board or committee will be required, and should also set a date for reevaluating the research project. In light of the risk/benefit ratio reassessment, the IRB may require that the research be modified or halted altogether. Alternatively, special precautions or criteria for inclusion may be relaxed. The principal investigator and study team will keep the IPEC IRB informed of significant findings that may affect the risk/benefit ratio. The investigators will inform patients of any important new information that might affect their willingness to continue participating in the research.

### Data collection

At the screening phase, data regarding quality of life, six-minute-walk test results, DRPs, and clinical and sociodemographic data will be collected. Clinical and sociodemographicdata will include age, sex, functional class, heart rate, blood pressure, weight, Chagas serological test results, biochemical data (urea, creatinine, bilirubin, aspartate aminotransferase, alanine aminotransferase, and alkaline phosphatase levels), and comorbidities (hypertension, diabetes, and asthma), as well as alcoholism, smoking, and prescription drugs.

Data about DRPs will be collected at least once a month. At the end of the study follow-up, DRPs, six-minute-walk test results and MLHFQ and SF-36 scores will be collected again.

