## Abstract

**Background:**

Pharmaceutical care is the direct interaction between pharmacist and patient, in order to improve therapeutic compliance, promote adequate pharmacotherapeutic follow-up, and improve quality of life. Pharmaceutical care may be effective in reducing complications and in improving the quality of life of patients with chronic diseases, like Chagas heart disease, while bringing a positive impact on health system costs. The morbidity and mortality indexes for patients with Chagas heart disease are high, especially if this heart disease is complicated by heart failure. In this setting, we hypothesize that pharmaceutical care might be an important tool for the clinical management of these patients by improving their quality of life, as a better compliance to their treatment and the avoidance and prompt correction of drug-related problems will minimize their symptoms, improve their functional class, and decrease the number of hospital admissions. Therefore, the aim of this trial is to evaluate the contribution of pharmaceutical care to clinical treatment of patients with Chagas heart disease complicated by heart failure.

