## Methods/design

### Study design

The proposed clinical trial will be held at a single center, the Evandro Chagas Clinical Research Institute (IPEC), which is one of the technical scientific units of the Oswaldo Cruz Foundation (Fiocruz). IPEC is a 93-year-old institution fully dedicated to clinical research in infectious diseases, including Chagas disease, among others. IPEC is a major reference center for research, care, and training on Chagas disease.

This is a double-blinded, controlled, superiority (parallel) clinical trial with balanced randomization [1:1] that will be conducted for adult volunteers with Chagas disease complicated by HF. The patients’ functional status will be classified according the New York Heart Association (NYHA) functional classification system from I to IV. All patients at our institution are treated following current guidelines for diagnosis and management of HF in adults [12].

The cardiologists from our outpatient center will refer patients with chronic Chagas disease complicated by HF to the pharmacist. The pharmacist will explain the study in detail and obtain the patients’ informed consent. All included patients will undergo a screening phase, which includes a review of the patient’s medical records and an interview for assessment of eligibility. All eligible patients will complete quality-of-life questionnaires and take a six-minute-walk test after inclusion. After the screening phase, patients will be randomly assigned to one of two groups: an intervention group, who will receive standard care plus pharmaceutical care, and a control group, who will receive only standard care.

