Each patient will be followed for 12 months. All patients from both groups will take part in medical consultations every month. After each medical consultation, a pharmacist blinded to the patient’s assignment will interview all patients, to identify compliance to treatment and any DRPs. After this, all patients will interact with the clinical pharmacist. Those randomized to the control group will receive all prescription medications, while those patients randomized to the intervention group will not only receive all prescription medications but will also undergo pharmaceutical care, to solve DRPs, confirm, and reinforce their compliance to the medical prescription. Whenever the pharmacist identifies a DRP in the intervention group, he will interact with the physician, to solve the DRP. All patients will take part in a pharmaceutical consultation at the end of the follow-up, to identify DRPs, complete quality-of-life questionnaires, and perform six-minute-walk tests. The pharmacists who will deliver the initial evaluation before randomization, the monthly evaluations of DRPs and compliance, and the final evaluation at the end of the follow-up period will be blinded to the patients’ assignment (Figure 1).

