### Sample size calculation

Sample size calculation was based on previous work of the literature that evaluated pharmaceutical care and quality of life in patients with HF [21]. We estimated that 40 patients per group would be needed to detect a difference in quality of life on SF-36 of 10.3 points, allowing a standard deviation of up to 10.9 points, one-sided 1% significance, and 95% power. As we expect loss during follow-up of at least 10% of the study participants, 88 participants (44 per group) will be required (Table 1).

**Table 1 T1:** Sample size calculation according to scenarios of benefit in terms of quality of life for patients

**Parameter**	**Groups**		**Sample calculation**
	**Control group**	**Intervention group**	
Quality of life, mean (standard deviation)	52.8 (10.9)	63.1 (10.1)	
Significance level	1.0%	1.0%	
Power of test	95.0%	95.0%	
*N*	40 patients	40 patients	
*N* + 10% (in each group)	44 patients	44 patients	
Ratio	1:1	1:1	
Total	44	44	88

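### With quality of life scored only at baseline and month 12, patients who die or are lost add no post-baseline information to the primary comparison

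*Protocol article*

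**What the plan says.** All points are from the protocol article.

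- **Baseline score** (Study design): "All eligible patients will complete quality-of-life questionnaires and take a six-minute-walk test after inclusion". This precedes randomization.
- **Later score** (Data collection): "At the end of the study follow-up, DRPs, six-minute-walk test results and MLHFQ and SF-36 scores will be collected again". Follow-up is 12 months: "Each patient will be followed for 12 months".
- **Contact in between** (Study design): "All patients from both groups will take part in medical consultations every month". After each consultation, "a pharmacist blinded to the patient’s assignment will interview all patients, to identify compliance to treatment and any DRPs". Quality of life is not part of that interview. Data collection lists only drug-related problems (DRPs) as monthly data.
- **Analysis** (Statistical methods): Student's t test for the questionnaires, or the Wilcoxon rank-sum test if the distribution is not normal. No covariate is named. On the analysis set: "The statistical calculations will be performed on an intention-to-treat basis, where patients will be analyzed as initially randomized".
- **Expected loss** (Sample size calculation): "As we expect loss during follow-up of at least 10% of the study participants". The requirement of 40 per group is raised to 44.
- **Severity of the disease** (Abstract, Background): "The morbidity and mortality indexes for patients with Chagas heart disease are high".

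**The concern.** The primary endpoint has one post-randomization measurement, while a secondary endpoint (DRPs) is recorded every month. Both named tests need a month-12 score, whether they are run on final scores or on changes from baseline. A patient without that score cannot enter them.

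In heart failure, patients who die or stop attending are likely to be sicker than those who stay. The Background section also cites evidence that pharmaceutical care reduces admissions and possibly deaths, so on the trial's own reasoning loss may differ by arm. When loss depends on both health and arm, comparing only patients with an observed score is biased. For example, if the intervention keeps very sick patients alive and attending, their low scores count in its mean while similar control patients are absent from theirs.

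The measurement schedule is fixed in the protocol. An analysis plan not shown could add a missing-data rule, but it could not recover interim scores that were never collected.

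**Working it through.** **1. The plan's own figure.** Inputs from Sample size calculation and Table 1: difference 10.3, SD 10.9, 1% significance, 95% power.

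n per group = 2 × SD² × (z_α + z_β)² / difference²

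- Two-sided 1%: 2 × 118.81 × (2.576 + 1.645)² / 106.09 = 39.9, so 40 as stated.
- One-sided 1%, as the text says: 2 × 118.81 × (2.326 + 1.645)² / 106.09 = 35.3, so 36. That mismatch is a separate matter.
- Inflation: 40 × 1.10 = 44 per group, 88 in total. The plan thus counts lost patients as adding nothing to the primary test.

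**2. Effect of loss on power.**

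| Loss | Patients per group | Power, two-sided 1% | Power, one-sided 1% |
|---|---|---|---|
| 10% | 44 × 0.90 = 39.6 | 94.8% | 97.0% |
| 20% | 44 × 0.80 = 35.2 | 91.8% | 94.9% |

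The lost numbers matter little. The issue is bias.

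**3. Bias, simple form.** If a fraction d of an arm is missing and those patients would score L points lower than the observed ones, the full-arm mean is the observed mean minus d × L. With the same L in both arms, the bias of the difference (intervention minus control) is (d_int − d_ctrl) × L. The article gives neither loss by arm nor L, so both are assumptions.

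- Equal loss, equal L: 0.
- 5% intervention, 15% control: −0.5 for L = 5, −1.0 for L = 10, −2.0 for L = 20.
- Losses swapped: the same sizes with a plus sign.

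**4. Bias with loss tied to the score.** Same assumed 15% versus 5%, normal scores, SD 10.9.

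- Worst patients missing: the observed mean rises by SD × φ(z_p)/(1 − p). Control: 10.9 × 0.2332/0.85 = 2.99. Intervention: 10.9 × 0.1031/0.95 = 1.18. The bias is 2.99 − 1.18 = 1.81 points, and 1.81/10.3 is about 17.5% of the target.
- Logistic dependence of loss on the score, with the intercept set to give 15% or 5% missing: slope 0.5 per SD gives 0.52 points, slope 1 gives 0.93, slope 2 gives 1.37.

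**5. Outer limits.** Take the Table 1 means (52.8 and 63.1) for observed patients, with 88 − 80 = 8 lost patients scored 0, the worst possible SF-36 value.

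- 4 lost per arm: 10.3 × 40/44 = 9.4.
- All 8 in the intervention arm: 63.1 × 36/44 − 52.8 = −1.2.
- All 8 in the control arm: 63.1 − 52.8 × 36/44 = 19.9.

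These are bounds, not forecasts.

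**6. What interim scores would recover.** Setting: the same 15% versus 5% split, logistic slope 1 per SD, and an assumed correlation of 0.5 to 0.7 between scores. Baseline adjustment plus interim scores removes nearly all the bias if loss depends on earlier scores. It removes about 35 to 60% if loss depends on the unseen month-12 score.

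**The case against.** **Intention-to-treat.** A reader might infer that the promised intention-to-treat analysis is broken and becomes a completers analysis. The article does not support this. It defines intention-to-treat as analysis by randomized arm, and that holds. Patients who stop the intervention but attend at month 12 are still analysed as randomized. No sentence excludes patients without a final score; that follows from the named tests and the inflation to 44.

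**Other post-randomization data.** A reader might also infer that nothing observed after randomization bears on a lost patient's quality of life. That is too strong. DRPs and compliance are recorded monthly, the Abstract links both to quality of life, and with the baseline scores they could support an imputation. They are still indirect.

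**Size.** The 15% versus 5% split is invented; the article gives no mortality rate and no loss by arm. The trial excludes NYHA class IV and comorbidities that limit survival. Even with the worst patients missing, the difference is 10.3 − 1.8 = 8.5. With 44 × 0.85 = 37.4 and 44 × 0.95 = 41.8 patients, the standard error is 10.9 × √(1/37.4 + 1/41.8) = 2.45. Power is then about 93% at two-sided 5% and about 87% at one-sided 1%. In that split the bias also runs against the intervention; only the reverse split would inflate the effect. All this stands and limits the weight of the point.

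**The remedy.** Baseline plus one final assessment is an ordinary design, and missing-data rules may sit in a document not shown. Interim scores do not define quality of life after death and do not fully correct loss that depends on the unseen score. These objections also stand. They do not change the fact that the schedule discards information available at visits already held.

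**Conclusion.** The point holds as a limitation of the measurement schedule and the unadjusted test, not as a contradiction within the protocol. The primary comparison rests on patients with an observed month-12 score, and those who die or are lost add no post-baseline quality-of-life information.

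If loss depends on health and differs by arm, the estimated difference is biased by about 0.5 to 1.8 points, in either direction. That range rests on an assumed 15% versus 5% loss, an SD of 10.9 and an assumed dependence of loss on the score. With equal losses of the same kind there is no bias. A bias of this size would seldom overturn the conclusion if the true effect is the planned 10.3 points; it matters more if the effect is smaller. The change is worth making because it is cheap and uncollected scores cannot be recovered later.

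**What to change.** 1. **Collect.** Have the blinded pharmacist give the SF-36 and MLHFQ at some of the existing monthly visits, for example months 3, 6 and 9.
2. **Analyse.** Make the month-12 contrast from a baseline-adjusted repeated-measures model, using all post-baseline scores, the primary analysis.
3. **Deaths.** Pre-specify a sensitivity analysis that ranks patients who die below all survivors. This needs no extra data collection.
4. **At the least.** If no visits are added, adjust the month-12 comparison for the baseline score already collected. This does less for patients with no later score, but costs nothing.

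The cost is a short amendment and 36 + 21 = 57 items per occasion, or 3 × 57 = 171 extra items per patient over three occasions. Staff time is a real consideration in a population that the Discussion describes as often illiterate. No new visits and no change in sample size are needed. The trial is already recruiting, so patients enrolled before the amendment would start at their next scheduled visit and have incomplete interim data. Bias is removed only in part if loss depends on the unobserved month-12 score.
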